**Intervention study design**

The study will be a **cluster randomized intervention trial,** with **cross-over design** carried out in three phases:

(1) a 3 month screening reinforcement phase during which the adherence to the admission and discharge MRSA screening protocols will be promoted and monitored monthly to achieve > 80 % compliance rate, application of isolation precautions to MRSA colonized patients will be measured and checked to achieve > 80 % compliance and the MRSA acquisition rate will be checked to lie within 95 % confidence limits of the projected 3% estimate. In addition, the length of stay per ward will be measured and checked for homogeneous distributions.

(2) a 5 month conventional detection test (standard care) phase during which MRSA screening will be performed by optimized conventional culture methods 6 days a week during working hours.

(3) a 5 month rapid detection test intervention phase during which admission MRSA screening will be performed by rapid PCR testing 7 days a week during working hours.

After eligible wards in each hospital have been checked to meet these inclusion criteria in phase (1), the sequential order of inclusion of eligible study wards in phase (2) and (3) will be randomly assigned within each centre by assigning a number to each ward and using a computer generated list of random numbers per study arm in each hospital so that one half of the wards will start phase (2) for the first 5 months and then phase (3) for the following 5 months whereas the other study wards will be “crossed-over” to follow the reverse sequence. No wash-out period will be used between phase (2) and (3). If the analysis of patient length of stay by ward indicates homogeneous distribution with markedly different median values between wards, stratified randomisation of wards within short/long (below/above pooled median) stay groups will be considered.

The planned study start date is: November 3rd, 2008 for the baseline observation and completion is planned on December 31st, 2009 (post-poned to end January, 2010 see addendum).

Admission screening: evaluation of patient sampling procedures:

During the entire study period (baseline and intervention phase), the infection control nurse responsible for the study will perform daily rounds in each of the study wards to ensure that screening of all newly admitted patients is being done systematically and without delay.

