The **primary analysis** will be based on Poisson regression two level model (individual patient and unit exposure) performed at each hospital level to assess the impact of the intervention on local incidence-density of MRSA nosocomial colonisation, and ajusted for four potentially confounding factors. The dependent variable will be endpoint 1 above. The ward level **independent variables** will include (1) **intervention arm**, (2) MRSA **colonisation pressure** (as determined by monthly proportion of MRSA colonisation-days/total patient-days among patients admitted during the preceding month in one particular ward), (3) **staff** **compliance with standard and isolation precautions** (as determined by a sample of 50 observations per ward/ trial period, including 25 care opportunities for patients under MRSA isolation precautions and 25 for patients cared for with standard precautions; see appendix 6 for precautions compliance monitoring procedure) (4) **antibiotic use** (as determined by cumulated number of Defined Daily Doses of J01 ATC class of antimicrobial drugs per monthly period) and (5) monthly bed occupancy rate.

Heterogeneity of effect by ward/hospital will be assessed. **To quantify the protective efficacy of the intervention** for the at risk population per centre, the adjusted Rate Ratio (and 95% confidence interval) of nosocomial MRSA acquisition will be calculated for the intervention arm in all study wards per hospital. Pooled analysis of average effect for both hospitals will be calculated. In case of significant heterogeneity between hospitals, hospital level will be added as covariate in the model.

**Secondary analyses** will include:

A. Logistic regression two level models (individual patient and unit exposure) will be performed at each hospital level to assess the impact of the intervention on local cumulated incidence of MRSA nosocomial colonisation. The dependent variable will be endpoint 6 above. The **independent variables** will include patient age, sex and the 5 independent ward level indicators as described above for the primary Poisson analysis.

Heterogeneity of effect by ward/hospital will be assessed. Pooled analysis of average effect for both hospitals will be calculated. In case of significant heterogeneity between hospitals, hospital level will be added as covariate in the model.

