C. The median process time intervals (endpoints 2-4 above) and number of missed isolation days (endpoint 5 above) will be compared by Wilcoxon tests for patients within the same unit/hospital between arms; median times (interquartile range) will be compared for each study phase and hospital.

D. In addition, monthly rates of endpoints 1, 6 and 7 will be plotted over time and interrupted time-series, segmented linear regression analysis of temporal trends per study periods will be performed for each hospital. The hypothesis to be tested is that there will be a significant drop in the level of rates from the beginning of the intervention compared to the baseline or control period, possibly associated with a negative change of slope due to a decreasing trend in the intervention period.

E. Diagnostic accuracy (clinical sensitivity and specificity) will be calculated for the rapid PCR test (MRSA GeneXpert, Cepheid) compared to conventional culture as gold standard based on all matched nasal swabs (N=3,700) tested in parallel during the 10 month trial period.

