**Sample size estimate.**

Based on the cumulated incidence endpoint and study hypothesis that shortening time to detection of MRSA carriage by 3 days will reduce MRSA nosocomial acquisition by 50%, a standard sample size calculation for detecting a difference in proportion between 3% and 1.5% in two independent samples with α=0.05 and ß=0.20 (80 % power) suggests that 1,237 patients should be included in each study arm. Assuming non-independence of samples due to the time dependence of MRSA transmission rates between study phases and taking into account the cluster design, a conservative 150 % sample size estimate would suggest enrollment of 1850 patients per arm in each hospital, or a total inclusion of 7,400 patients.

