# Two-Center Intervention Study to Evaluate the Impact of Rapid Molecular Screening on Nosocomial Transmission of Methicillin-Resistant *Staphylococcus aureus* (MRSA).

# Addendum 1 to the protocol – modification of analysis plan (February 7th, 2009)

Based on the results of the base-line period (November 3rd, 2008 –January 15th, 2009), 7 wards of Erasme hospital and 6 wards of AZ St Jan hospital have been randomized and allocated either to the intervention or control arm for the first 5 month study period to begin on February 9th, 2009. Stratified randomization of wards was performed according to the hospital and average patients’ length of hospital stay.

In the base-line period, the compliance rates with key processes of care were achieved (admission screening cultures and infection control precautions > 80%) or closely approached (discharge screening cultures 68% and improving during the baseline weeks). However, the incidence of MRSA nosocomial acquisition was lower than hypothesized in the protocol: 0.79% (95%CI: 0.34% - 1.55%). This incidence rate was unexpectedly low compared to previously recorded rates. When considering the higher limit of the 95%CI, the planned sample size allows detection of a 50% reduction in incidence of nosocomial acquisition with 80% power and taking into account a potential cluster effect only if the pooled incidence in both hospitals combined is analysed as the primary endpoint. Therefore, although heterogeneity between the two hospitals will be studied as planned, the pooled results for both hospitals will be presented and analysed as the primary endpoint.

An additional interim analysis is planned three months after the beginning of the study to obtain a new estimate of the incidence of MRSA nosocomial acquisition in the control units and to check if the number of subjects is large enough to reach the objectives.

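### The patient-level Wilcoxon tests in secondary analysis C allow neither for correlation within ward-periods nor for period, so their p-values can be too small

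*Protocol*

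**What the plan says.** Under Study endpoints and statistical analysis, item C of the secondary analyses covers the process time intervals and the number of missed isolation days. These "will be compared by Wilcoxon tests for patients within the same unit/hospital between arms", and "median times (interquartile range) will be compared for each study phase and hospital". No ward-period term and no period adjustment is named.

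The rest of the protocol treats the ward as a source of correlation:

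- **Design** (Intervention study design): wards are the randomised units and each serves in both arms, since "one half of the wards will start phase (2) for the first 5 months" and then switches, while the others follow the reverse order. Addendum 1 reports that "7 wards of Erasme hospital and 6 wards of AZ St Jan hospital have been randomized", stratified by hospital and average length of stay.
- **Primary analysis:** a "Poisson regression two level model (individual patient and unit exposure").
- **Secondary analysis A:** "Logistic regression two level models (individual patient and unit exposure").
- **Sample size estimate:** "Assuming non-independence of samples due to the time dependence of MRSA transmission rates between study phases and taking into account the cluster design", the protocol inflates by half.

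**The concern.** Analysis C answers secondary aims 1 to 3: time to detection, time to isolation, and days that carriers spend unisolated. Faster isolation is a general objective of the study and the presumed route to fewer acquisitions.

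A patient-level Wilcoxon test takes patients as independent. Yet patients in the same ward and the same five months share staffing, occupancy and single-room supply. Appendix 3 makes isolation depend on the ward nurse and on whether a single room is available. The primary model already includes monthly bed occupancy and colonisation pressure, and compliance per ward and trial period, so the protocol itself expects wards to change over time.

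The phrase unit/hospital does not settle how the test is run. Run ward by ward, each test compares one ward's two phases, so arm and period coincide. Pooled or stratified within a hospital, the test still treats patients in a ward-period as independent. In either case a modest difference in time to isolation or in unisolated days could be called significant too readily.

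**Working it through.** **The plan's own figures.** None is given for these endpoints. The only allowance for clustering is the factor in the sample size: 1,237 × 1.5 = 1,855.5, rounded to 1,850 per arm per hospital; 1,850 × 2 arms × 2 hospitals = 7,400. This matches the protocol. If 1.5 were also the design effect here, the true error of a nominal 5% test would be 2[1 − Φ(1.96/√1.5)] = 0.11. That is an illustration only, because the factor was set for acquisition rates.

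**Inputs.**
- Wards: 7 + 6 = 13, hence 26 ward-periods (Addendum 1).
- Carriers per ward-phase: not given. The budget's 200 typed isolates give 200/26 ≈ 8. An assumed 4% of 3,700 patients per arm gives 148/13 ≈ 11. The range examined is 8 to 20.
- Intraclass correlations: not given. Assumed shares of total variance are 0.05 to 0.10 for stable ward differences and 0 to 0.05 for ward-by-period variation.

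**Simulation under no PCR effect** (normal data, nominal two-sided 5%, 13 wards). Entries are rejection rates. With 1,500 runs the Monte Carlo standard error is about √(0.05 × 0.95/1,500) = 0.006; the rows with 8 carriers used 3,000 runs. Equal ward-phase sizes unless stated.

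| Carriers per ward-phase | Stable share | Ward-by-period share | Pooled Wilcoxon | Ward-stratified Wilcoxon | Wilcoxon per ward | Ward-level t-test by sequence |
|---|---|---|---|---|---|---|
| 10 | 0.05 | 0 | 0.053 | 0.049 | 0.053 | 0.055 |
| 20 | 0.05 | 0 | 0.043 | 0.047 | 0.049 | 0.050 |
| 8 | 0.05 | 0.02 | 0.058 | 0.067 | 0.065 | 0.049 |
| 20 | 0.05 | 0.02 | 0.092 | 0.103 | 0.095 | 0.060 |
| 8 | 0.05 | 0.05 | 0.085 | 0.086 | 0.094 | 0.054 |
| 20 | 0.05 | 0.05 | 0.137 | 0.139 | 0.163 | 0.045 |
| mean 15, sizes vary (CV 0.6) | 0.10 | 0 | 0.101 | 0.048 | 0.049 | 0.053 |
| mean 15, sizes vary (CV 0.6) | 0.05 | 0.05 | 0.185 | 0.139 | 0.119 | 0.051 |
| 15, period shift 0.3 SD | 0.05 | 0 | 0.050 | 0.052 | 0.131 | 0.051 |

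**At 11 carriers per ward-phase, 13 wards:**
- stable ward differences only: pooled 0.04, stratified 0.05;
- ward-by-period share 0.02, equal sizes: pooled 0.06;
- ward-by-period share 0.05, equal sizes: pooled 0.08, stratified 0.10;
- ward-by-period share 0.05, unequal sizes: pooled 0.18, stratified 0.12.

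**Reading.** Three conditions inflate the error: ward-by-period variation (all patient-level versions), unequal ward-phase sizes when wards are pooled, and a period effect when tests are run per ward. Without them the patient-level tests hold their level.

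**The case against.** A reader might infer that analysis C disregards the ward altogether and that its p-values must be too small. The documents do not support this. The comparison is made within the unit, and in a cross-over that can cancel stable ward differences. A ward-stratified test is a natural reading of the text. With stable differences only and equal ward-phase sizes, every patient-level version stayed near 5%. This part of the objection stands.

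The size also rests on assumptions. A parallel-cluster design effect, 1 + (m − 1)ICC, would charge the whole correlation to the ward-phase. If a total of 0.05 splits into 0.04 stable and 0.01 ward-by-period, the simulated error at 11 carriers is 0.055; a total of 0.10 split 0.08 and 0.02 gives 0.068. This stands as well: the inflation may be small.

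A reader might also infer that C is the only analysis without a ward term. It is not: the time series in D and the diagnostic accuracy in E name none either.

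Finally, these are secondary endpoints, and the protocol plans on unisolated stay falling from 3 days to 0. A gain that large, or a large gain in notification time, would survive any test. That limits the consequence but does not make the test valid. Its level depends on the absence of ward-by-period variation, together with balanced sizes if pooled or no period effect if run per ward. The protocol secures none of these, and wards that mix intensive care, medical, surgical and geriatric patients are unlikely to be equal in size.

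**Conclusion.** The point holds in conditional form. Analysis C fixes a patient-level test that allows neither for correlation within ward-periods nor for period, which does not match the randomisation, the two-level models or the stated non-independence. Its p-values can be too small; the documents do not show that they must be.

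Assuming about 11 carriers per ward-phase and a ward-by-period share of 0.02 to 0.05, the true error of a nominal 5% test is roughly 6% to 10% with equal ward-phase sizes. It is about 12% to 18% at 0.05 with unequal sizes. The carrier count, the variance shares and the spread of sizes are all assumptions. The consequence is confined to secondary aims 1 to 3, chiefly to modest differences in time to isolation and unisolated days. The primary conclusion is not affected.

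**What to change.** Replace the test in C as follows.

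1. For each ward and period, compute the median of each process time and the mean unisolated days per carrier.
2. For each ward, take period 2 minus period 1.
3. Compare these 13 differences between the two randomised sequences, stratified by hospital and length of stay, with a t-test or a stratified permutation test.
4. Report half the difference between sequences (culture-first minus PCR-first) with a 95% CI. With period effect π and PCR effect δ, the expected ward difference is π + δ for culture-first wards and π − δ for PCR-first wards. Their difference is 2δ and π drops out. This assumes no carry-over, which the wash-out month in Addendum 2 supports.

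Make this one test pooled over both hospitals, in line with Addendum 1. Keep patient-level medians (IQR) by hospital and phase as description. A mixed model with random effects for ward and ward-period and a fixed period term is an alternative, and is easier where a ward-phase has few carriers.

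A signed-rank test on PCR-minus-culture differences looks simpler but leaves period in. Its error fell to 0.01 with a period shift of 0.5 SD and to 0.00 with 1.0 SD, so it loses sensitivity. The sequence comparison, simulated without strata, held 0.04 to 0.06 throughout.

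**Cost:** a few sentences and no new data. Intervals will be wider, and ward medians from about 11 carriers are noisy. Hospital-specific tests will have little power: with 6 wards split 3 and 3 there are 20 allocations, so an unstratified two-sided permutation p cannot fall below 2/20 = 0.10.

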**Secondary aims:**

To compare the following secondary outcomes during periods of MRSA carrier screening among hospital admissions by means of rapid PCR testing versus conventional culture:

1. Median time required for detection of MRSA carriage after admission
2. Median time required for starting isolation of MRSA carriers
3. Number of patient-days of MRSA carrier stay in non-isolated conditions
4. MRSA nosocomial infection rate
5. MRSA cross-transmission rate
6. Sensitivity and specificity of PCR vs conventional MRSA screening

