**Secondary endpoints**

These will include three related process of care indicators:

1. Time (h) between admission and notification of MRSA positive culture/PCR
2. Time (h) between admission and placement of newly detected MRSA carrier in contact isolation

Secondary endpoints will also include the following microbiologically-documented outcomes:

1. Number of patient-days of MRSA positive patients cared for with standard precautions and not isolated
2. Cumulative incidence of MRSA nosocomial colonisation, defined as number of new cases of hospital-acquired MRSA (first positive culture >48 h after admission) divided by the number of admitted patients who stayed ≥ 3 days and were MRSA negative on admission by culture and PCR testing, if performed.
3. Cumulative incidence of MRSA nosocomial infection, defined as number of new cases of hospital acquired MRSA infection (according to CDC definitions for nosocomial infection and with first MRSA positive culture > 48 h after admission) divided by number of admitted patients who stayed ≥ 3 days.
4. Number of clusters of ≥ 2 cases/unit of acquired MRSA colonisation with a clonally related strain, defined as a MRSA strain with the same spa type or PFGE major type.
5. Sensitivity and specificity of rapid PCR test compared to conventional culture for MRSA screening, taking into account one parallel set of admission nasal screening samples per patient.

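### Secondary aim 4 asks for PCR versus culture on MRSA infection, but the only analysis named for infection is a per-hospital time series that largely bypasses the randomised comparison

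*Protocol*

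**What the plan says.** The Secondary aims section of the protocol sets out "To compare the following secondary outcomes during periods of MRSA carrier screening among hospital admissions by means of rapid PCR testing versus conventional culture", and the fourth item on that list is "MRSA nosocomial infection rate". Under Secondary endpoints the outcome is defined: "Cumulative incidence of MRSA nosocomial infection, defined as number of new cases of hospital acquired MRSA infection" per admitted patient staying at least three days.

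The Intervention study design section randomises the order of screening methods by ward: "one half of the wards will start phase (2) for the first 5 months and then phase (3) for the following 5 months", and the remaining wards take the reverse order. Addendum 1 reports 7 wards randomised at one hospital and 6 at the other. Addendum 2 inserts a one-month wash-out before the crossover.

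The analyses refer to endpoints by number. The primary two-level Poisson model takes endpoint 1 and has an intervention-arm term. For secondary analysis A, a two-level logistic model with the same arm term, "The dependent variable will be endpoint 6 above". Analysis C compares endpoints 2-5 between arms by Wilcoxon tests. Analysis D, done hospital by hospital, reads: "monthly rates of endpoints 1, 6 and 7 will be plotted over time and interrupted time-series, segmented linear regression analysis of temporal trends per study" (quotation shortened). Its hypothesis is a drop in level when the intervention begins, relative to either baseline or the control period. Analysis E concerns the accuracy of the PCR test. There is no item B.

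**The concern.** Infection is the only clinical outcome among the endpoints; the others measure colonisation, process times, missed isolation days, clusters or test accuracy. The aim is worded as a comparison of screening methods, and the randomised data needed for it are collected. Yet the one method and hypothesis that the protocol fixes for infection is a segmented regression on monthly hospital rates.

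That method suits a hospital that switches from one policy to another on a single date. Here, half the wards use PCR and half use culture in each trial period. A hospital series has no single start of intervention and no separate control period. Two things follow if D is read as one series per hospital. A real PCR effect is diluted at trial start and nearly cancels at the crossover. A change common to all wards after the three-month reinforcement phase is indistinguishable from a PCR effect. The protocol's own Introduction names uncontrolled before-after designs as a source of bias in the existing literature.

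**Working it through.** **1. Which endpoint is number 7.** Numbering restarts within the Secondary endpoints list, and the section announces a third process indicator ("These will include three related process of care indicators") where two are shown, so the number has to be inferred. A running count gives 1 = incidence density of colonisation, 2-4 = process times, 5 = patient-days not isolated, 6 = cumulative incidence of colonisation, 7 = cumulative incidence of infection. Two cross-references confirm it: analysis C calls missed isolation days endpoint 5, and analysis A uses endpoint 6 for cumulative colonisation. Infection is the next item.

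**2. Which analysis covers which endpoint.**

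| Endpoint | Between-arm analysis | Analysis D |
|---|---|---|
| 1 colonisation density | primary Poisson model | yes |
| 2-5 process times, missed isolation days | C | no |
| 6 cumulative colonisation | A | yes |
| 7 infection | none named | yes |

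**3. What a hospital series would show.** Assume equal ward sizes and a true ward-level rate ratio of 0.5. The 50% is the protocol's effect size for acquisition, borrowed here for illustration. With w wards, of which f start on PCR, the expected hospital rate relative to control is

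- first period: 1 − 0.5 × f/w
- second period: 1 − 0.5 × (w − f)/w

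| Wards (PCR first) | First period | Second period | Second ÷ first |
|---|---|---|---|
| 6 (3) | 0.750 | 0.750 | 1.00 |
| 7 (4) | 0.714 | 0.786 | 1.10 |
| 7 (3) | 0.786 | 0.714 | 0.91 |

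A halving at ward level therefore gives a ratio of 0.91 to 1.10 at the crossover, and a drop of only 21% to 29% from baseline.

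**4. Chance that D detects it.** Simulated series per hospital used 370 at-risk admissions a month (3,700 over 10 months), 3 baseline months, 5 months, a one-month gap and 5 months, with ordinary least squares for level and slope changes. The assumed infection rate was 0.3% to 0.79%. With PCR halving the rate, a significant drop appeared at trial start in about 6% to 7% of runs, and at the crossover in about 2.5%, which is the nominal level in that direction. With no change at all, a drop at trial start appeared in 3.2% to 3.7%. With a purely hypothetical 50% fall shared by all wards and no PCR effect, it appeared in about 10% to 15%.

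**5. What the randomised comparison could offer.** The protocol gives no infection rate, so p₁ is assumed at 0.3% to 0.79%, with p₂ = p₁/2. Pooled n per arm is 2 × 1,850 = 3,700. Dividing by the protocol's 1.5 inflation gives an effective n of 2,467. The two-sided 5% test has

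power = Φ{[(p₁ − p₂) − 1.96 √(2p̄(1 − p̄)/n)] / √([p₁(1 − p₁) + p₂(1 − p₂)]/n)}, where p̄ = (p₁ + p₂)/2.

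- p₁ = 0.3%: (0.00150 − 1.96 × 0.001349)/0.001349 = −0.85, power 0.198
- p₁ = 0.5%: power 0.300
- p₁ = 0.79%: (0.00395 − 1.96 × 0.002185)/0.002185 = −0.15, power 0.439

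For a single hospital (n = 1,850/1.5 = 1,233) the range is about 0.12 to 0.25. Expected infections in total are 3,700 × (0.003 + 0.0015) ≈ 17 to 3,700 × (0.0079 + 0.00395) ≈ 44.

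**The case against.** A reader might infer that the protocol never compares infection between the arms. The text does not support that. The aim itself commits to the comparison "during periods of MRSA carrier screening among hospital admissions by means of rapid PCR testing versus conventional culture"; what is missing is a specified between-arm method. The list of analyses is introduced as inclusive, not exhaustive, and jumps from A to C. An item may have been dropped, and the document cannot show whether it covered infection. The cluster endpoint is named in no analysis either, which also points to an incomplete list. A statistical analysis plan not shown here could supply the model.

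D is also not wholly settled. It is segmented by study period and mentions the control period, so series aligned to each ward's own switch would contrast PCR with culture within wards. The dilution in the working applies to the hospital-level calendar reading.

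Nor may one argue that a large fall after baseline is likely because Addendum 1 reports 0.79% against a projected 3%. The 0.79% was observed during baseline, concerns acquisition, and fell short of a projection; it shows no fall after baseline. It is not an upper bound for the infection rate either, since its 95% confidence interval is 0.34% to 1.55%. The 10% to 15% figure therefore illustrates a hypothetical, not an expected error rate.

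Finally, the randomised comparison would itself be underpowered. That is true, but low power does not make a time contrast a better answer to a question about arms. What remains is that the protocol is not silent on infection. It fixes a method and a hypothesis that, read plainly, do not use the randomisation.

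**Conclusion.** The concern holds in this form: no between-arm analysis is specified for infection, although aim 4 calls for one and endpoints 1, 2-5 and 6 have one. The only named analysis, read as one calendar series per hospital, would show almost none of a PCR effect at the crossover. Against baseline it would show a 21% to 29% drop for a true halving, mixed with any shared change. Those figures assume equal ward sizes and a rate ratio of 0.5. The power and simulation figures also rest on an assumed infection rate of 0.3% to 0.79%.

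This is worth correcting because the correction is cheap and uses data already collected. It concerns one secondary aim.

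**What to change.** Add a separate secondary analysis, for example as item B:

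- Fit a two-level model to endpoint 7 with intervention arm and design factors only (period, ward, hospital). Simply adding endpoint 7 to analysis A would bring in age, sex and four further ward-level covariates besides arm, too many for roughly 17 to 44 events.
- Pool both hospitals, as Addendum 1 does for the primary endpoint.
- Report the PCR-versus-culture odds or rate ratio with its 95% confidence interval as the result for aim 4.
- Label analysis D descriptive for infection.
- If an item B was dropped, restore it or relabel the list, and number the endpoints consecutively so that the cross-references are unambiguous.

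The cost is a short paragraph and one more model, with no new data. The downside is a wide confidence interval, which the protocol should acknowledge in advance.

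### Analysis D, read as a hospital-level time series, has no control-to-intervention switch and can show only a diluted step from baseline or from the wash-out month

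*Protocol*

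**What the plan says.** Item D of the secondary analyses (Protocol, Study endpoints and statistical analysis) first states that "monthly rates of endpoints 1, 6 and 7 will be plotted over time". By the numbering that items A and C imply, these endpoints are the incidence density of acquisition (the primary endpoint), its cumulative incidence, and the cumulative incidence of MRSA infection. D then fixes the method and the unit: "segmented linear regression analysis of temporal trends per study periods will be performed for each hospital". Its hypothesis reads: "there will be a significant drop in the level of rates from the beginning of the intervention compared to the baseline or control period". A downward change of slope may accompany this.

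The subsection Intervention study design sets the allocation. The order of the two test phases "will be randomly assigned within each centre by assigning a number to each ward". As a result, "one half of the wards will start phase (2) for the first 5 months and then phase (3) for the following 5 months". For the rest, "the other study wards will be “crossed-over” to follow the reverse sequence". Both are preceded by "a 3 month screening reinforcement phase" that uses conventional culture.

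Addendum 1 reports that 7 wards at one hospital and 6 at the other were randomised, and that baseline data ran from November 3rd to January 15th. Addendum 2 inserts one month between the two trial periods in which no ward uses PCR. Addendum 1 is titled as a modification of the analysis plan, but neither addendum changes D.

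**The concern.** An interrupted time series needs a date at which the unit under study passes from control to intervention. Here that date exists for a ward, or for a group of wards sharing a sequence. It does not exist for a hospital, because the two groups cross in opposite directions. A hospital-level series mixes culture wards and PCR wards in similar proportions in both trial periods, so the ward-level effect cancels between them.

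D is applied to the primary endpoint's rate as well as to two secondary ones, so its result will be read alongside the main result. A flat hospital series could be taken as evidence against PCR, and a step after baseline as evidence for it. Neither inference would be sound.

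**Working it through.** The plan gives no numerical figure for analysis D, so there is none to reproduce. The check asks what a hospital-level series would be expected to show if the intervention worked as hypothesised.

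**Inputs**
- Wards randomised: 6 and 7 (Addendum 1).
- Effect: 50% reduction, rate ratio 0.5 (Primary aim; Sample size estimate).
- Planned patients: 3,700 per hospital over 10 trial months (Study type and patient population), so 3,700 / 10 = 370 per month.
- Baseline incidence: 0.79%, 95% CI 0.34% to 1.55% (Addendum 1); planning value 3%.
- Assumptions: equal wards, no carry-over into the wash-out, and the pooled incidence applied to each hospital.

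**Expected hospital rate**

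With f the share of wards on PCR, the rate relative to control is 1 − 0.5 × f.

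| Hospital | Baseline | Period 1 | Wash-out | Period 2 |
|---|---|---|---|---|
| 6 wards: f | 0 | 3/6 | 0 | 3/6 |
| 6 wards: rate | 1 | 0.75 | 1 | 0.75 |
| 7 wards: f | 0 | 3/7 | 0 | 4/7 |
| 7 wards: rate | 1 | 0.79 | 1 | 0.71 |

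For 7 wards the trial periods may be the other way round (1, 0.71, 1, 0.79); the document does not say which.

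- Period 1 to period 2, 6 wards: 0.75 / 0.75 = 1, a change of 0%.
- Period 1 to period 2, 7 wards: 0.714 / 0.786 = 0.91, or 0.786 / 0.714 = 1.10, a change of about 10% in either direction.
- Baseline or wash-out to a trial period: 1 − 0.786 = 21%, 1 − 0.75 = 25%, or 1 − 0.714 = 29%.
- A ward or sequence group at its own switch: the full 50%.

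**Case numbers per hospital-month** (all wards on culture; then × 0.75 with half on PCR)
- At 0.34%: 370 × 0.0034 = 1.3; 0.9
- At 0.79%: 370 × 0.0079 = 2.9; 2.2
- At 1.55%: 370 × 0.0155 = 5.7; 4.3
- At 3%: 370 × 0.03 = 11.1; 8.3

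**Chance of a significant drop in level**

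A segmented linear regression (intercept, slope, level change, slope change; two-sided 5% test, drops only counted) was simulated with binomial variation alone, 4,000 series per setting.

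| Series | 3% | 1.55% | 0.79% |
|---|---|---|---|
| Hospital, 3 baseline + 5 trial months, half the wards start PCR | 8% | 6% | 5% |
| Same, if all wards started PCR | 19% | 13% | 10% |
| Hospital, period 1 to period 2 (5 + 5 months) | 3% | 2.5% | 2.5% |
| Culture-first wards only, 5 + 5 months, 185 patients per month | 16% | 10% | 7% |

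The third row is the false-positive rate in one direction: there is no signal to find. The first row uses three full baseline months. The reported baseline window is about two and a half months, so the real series has at most two or three points from which to fit a pre-intervention level and slope.

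**The case against.** The strongest reply is that performing the regression for each hospital may mean stratifying by hospital, not pooling its wards. The primary and logistic models are also run at hospital level, yet carry arm as a ward-level variable. Phases (2) and (3) are defined by the test used, and D's hypothesis speaks of a control period and an intervention period, which in this design exist only for a ward or sequence group. How the series is built might also be left to a statistical analysis plan that is not shown.

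This reading is possible, but D does not state it. Item C compares arms explicitly, whereas D names no arm, ward or sequence. Addendum 1 uses the term study period for a calendar period. The Protocol itself fixes D's unit, method and hypothesis, so this is more than detail left for later. Splitting by arm would not be enough either, because different wards make up each arm before and after the crossover.

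Two stronger conclusions are tempting, and the document supports neither:
- A reader might infer that the hospital series has no intervention start at all, so that the hypothesis cannot be tested. But the share of wards on PCR rises from zero to about half after baseline, and again after the wash-out month, and the hypothesis names baseline as one of its comparators. The step is diluted and weakly powered, not absent.
- A reader might infer that any fall after baseline would be mostly secular or ascertainment change. Nothing in the document shows that. Discharge screening stood at 68% and was improving, and the Protocol assumes that adding it doubles detection. Better ascertainment would therefore raise detected cases and could mask a drop.

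It also stands that D is a supplementary analysis, and that using a count model in place of linear regression is a preference, not the remedy for this defect.

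**Conclusion.** The point holds for D read as a hospital-level series, which is its plainest reading. On that reading there is no control-to-intervention switch: the contrast between the two trial periods is 0% (6 wards) or about 10% in either direction (7 wards), against 50% at ward level. Only a step of about 21–29% remains, measured from a short baseline or from the single wash-out month. The baseline step had a simulated chance of detection of about 5–8%. It is also an uncontrolled before-after comparison, a design whose bias the Introduction itself notes, and it is mixed with compliance reinforcement and changing discharge screening.

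The sizes rest on a rate ratio of 0.5, equal wards and no carry-over into the wash-out. The detection chances also rest on 370 patients per hospital-month and binomial variation only. Unequal wards would move the figures but would not create a hospital-wide control period within the trial. The primary Poisson model takes intervention arm at ward level and is not affected. The wording should be changed, but the point does not threaten the main result.

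**What to change.** Reword item D so that the monthly series are built by randomised sequence group (culture-first wards and PCR-first wards), within hospital or stratified by hospital. Place the break at that group's own start of PCR, or at its stop for the PCR-first wards, and code the wash-out month separately. Preferably model monthly counts with an offset matching each endpoint's denominator: patient-days for endpoint 1, and patients at risk for endpoints 6 and 7.

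If this is thought too thin to test, limit D to descriptive monthly plots by sequence group. In either case, do not test a level change on the hospital-aggregated series.

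The cost is one reworded paragraph and slightly more analysis on the same data. The downside is fewer cases per series. For culture-first wards in one hospital, the simulated chance of detecting the level drop is still only about 7–16%. Regrouping makes the contrast interpretable but does not make it well powered, which is an argument for the descriptive version.
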